### Randomization

Once the men have consented to participate in the study and the baseline measurements are carried out, they are randomly allocated to one of the three study groups. A randomization list based on random numbers is made and transferred to sequentially numbered sealed envelopes.

### Sample size

Sample sizes were calculated by statistical power analysis. We hypothesised that the percentage of men continuing the increased exercise level after one year would be 30% in the control group and 50% in the exercise group. To detect this difference with α = .05 and β = .80, 91 men in each group are needed.

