**Methods/design:**

During a two-year period we recruit 300 men aged from 35 to 45 years with elevated cardiovascular risk (> two traditional risk factors). The men are randomized into three arms: 1) a health promotion intervention alone, 2) both health promotion and exercise intervention, or 3) control with usual community care and delayed health promotion (these men receive the intervention after one year). The main outcome measures will be the existence of metabolic syndrome and physical activity frequency (times per week). The participants are assessed at baseline, and at 3, 6, and 12 months. The follow-up of the study will last 12 months.

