### Outcome measures

The outcomes are measured after 3, 6 and 12 months of the randomization. The blood tests are taken at months 0, 3 and 12. Other outcomes are measured by Internet surveys and, if the participant does not respond, by telephone surveys.

Primary outcome measures will be 1) metabolic syndrome defined by International Diabetes Federation/American Heart Association
[11], thus fulfilling three or more of the following criteria:

- systolic blood pressure ≥ 130 or diastolic blood pressure ≥ 85 or specific medication;

- triglyserides ≥1.7 mmol/L or specific medication;

- HDL cholesterol < 1.0 mmol/L or specific medication

- fasting plasma glucose ≥ 5.6 mmol/L or specific medication;

- waist circumference >94 cm

2) and self-reported physical activity measured by how many times per week a participant performs vigorous exercise activity. Table 
1 shows also the secondary outcome measures.

**Table 1 T1:** Outcome measures

**Variable**	**T0**	**T1**	**T2**	**T3**
1. Primary outcome measures				
1.1 Metabolic syndrome1 (yes/no)	x	x	x	x
● Blood pressure, waist circumference,				
● Blood LDL- and HDL-cholesterol, triglycerides, blood glucose				
1.2 Physical activity	x	x	x	x
● Self-reported physical activity, exercise times, per week				
2. Other outcome measures				
● 2 km walking test (s)	x	x		x
● Self-reported general health (0–100)	x	x	x	x
● Self-reported overall stress (0–100)	x	x	x	x
● Utilisation and costs of medical services	x	x	x	x
● Individual cardiovascular risk factors: total cholesterol (mmol/L), LDL-cholesterol (mmol/L), HDL-cholesterol (mmol/L), smoking (yes/no), blood glucose (mmol/L), hs-CRP (mmol/L)	x	x	x	x
	x	x		x
● Body composition (InBody): muscle mass (kg), body fat mass (kg)	x	x		x

1 Defined by International Diabetes Federation/American Heart Association
[11].

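### The 91-per-group calculation is arithmetically sound but prints power as β and rests on an undefined, unlisted endpoint, so 80% power is not shown for either primary outcome as specified

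*Protocol article*

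**What the plan says.** The Sample size section of the protocol article sizes the trial on a proportion: "We hypothesised that the percentage of men continuing the increased exercise level after one year would be 30% in the control group", with 50% in the exercise group. It concludes: "To detect this difference with α = .05 and β = .80, 91 men in each group are needed".

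The Outcome measures section and Table 1 name two primary outcomes. One is metabolic syndrome, yes or no, on three or more of five criteria. The other is "self-reported physical activity measured by how many times per week a participant performs vigorous exercise activity". The Abstract gives the same pair. Neither the primary nor the other outcomes in Table 1 include the proportion of men who continue an increased exercise level, and no section says what counts as increased or as continuing.

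Four other places bear on the point:
- Men who already exercise at least 30 minutes three or more times a week are excluded (Exclusion criteria).
- Controls are offered the interventions only after the 12-month follow-up (Control group).
- Participants are assessed at baseline and at 3, 6 and 12 months (Abstract), and Table 1 shows physical activity at all four times.
- The Discussion explains the choice of physical activity as a main outcome by the health gain expected in men who keep up a higher activity level.

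**The concern.** The calculation and the outcome list do not describe the same quantity. The sample size is for a yes/no responder, whereas the physical activity outcome is a weekly frequency and the other primary outcome is a different condition altogether. The responder wording also fits the control arm poorly: controls receive no programme before month 12, so they have no programme-induced increase to continue, and it is unclear what the 30% measures. In addition, the printed β is the power under the wrong name.

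What is at stake is how a null result is read. This is the only sample-size reasoning in the document. A reader who sees 91 per group at 80% power may take a null finding on metabolic syndrome or weekly frequency as coming from a trial powered for it. No such calculation is shown.

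**Working it through.** **Inputs from the protocol article.** Rates of 30% and 50%; α = .05 (sidedness not stated; two-sided reproduces the figure); a printed β of .80; 91 per group; 300 men in three arms (Abstract). The article gives no metabolic syndrome rate, and no mean, SD or target difference for weekly frequency.

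**1. Reproduce 91.** Unpooled normal approximation for two proportions, two-sided α = .05, power .80:

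n = (z₀.₉₇₅ + z₀.₈₀)² × [p₁(1−p₁) + p₂(1−p₂)] / (p₁−p₂)²
= (1.960 + 0.842)² × (0.21 + 0.25) / 0.20² = 90.3, so **91**.

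The pooled formula gives 93. Variants that do not fit are continuity-corrected (103), one-sided (74) and 90% power (124). The stated number is therefore sound for power .80. By the pooled formula, 91 per group gives 79.1% power. With 100 per group (300/3, equal allocation assumed) it is 82.8%.

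**2. Take β = .80 literally.** Power is then .20 and its z value is −0.842:

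n = (1.960 − 0.842)² × 0.46 / 0.04 = 14.4, so **15** (pooled: 16).

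Only power .80 is compatible with 91, so the printed symbol is a labelling error.

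**3. Weekly exercise frequency at 91 analysed men per arm.** The two-sample t-test has 80% power at a standardised difference of **0.42 SD** (normal approximation: √(2 × 2.802²/91) = 0.415; t-based: 0.418). For 0.3, 0.4 and 0.5 SD, power is 53%, 77% and 92%. The Statistical analysis section also allows a non-parametric test, so these figures are a guide.

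**4. Metabolic syndrome at 91 analysed men per arm.** Control rates are assumed over 30–70%. The smallest fall detectable with 80% power is:

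| Assumed control rate | Intervention rate | Absolute fall |
|---|---|---|
| 30% | 13% | about 17 points |
| 40% | 21% | about 19 points |
| 50% | 30% | about 20 points |
| 60% | 40% | about 20 points |
| 70% | 50% | about 20 points |

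Over the same range a 10-point fall would have 27–34% power at 91 per arm and would need 294–388 men per arm (pooled formula).

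**5. What the 30% v 50% hypothesis could imply for weekly frequency.** Assume the responder is a cut-off on a normal score with equal SDs. The implied difference is z₀.₅₀ − z₀.₃₀ = 0 + 0.524, or about 0.52 SD. At 91 per arm a t-test then has about 94% power. This is an illustration only, because the article gives no cut-off.

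**The case against.** The strongest reply is that the physical activity outcome is covered in substance. The Discussion ties that outcome to men who sustain a higher activity level, so the sized endpoint is most naturally a dichotomy of the same 12-month construct. Sizing on a dichotomy is usually conservative: under the assumption in step 5, the implied 0.52 SD exceeds the detectable 0.42 SD. This stands as far as it goes. Support for weekly frequency is indirect rather than absent, and 0.42 SD is not evidence of a shortfall. But the link needs a cut-off or an SD, and the article gives neither. The reply also does nothing for metabolic syndrome.

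A reader might infer that the endpoint cannot be defined for controls. The document does not support that. Activity is measured at baseline and 12 months with no arm exempted, and excluding active exercisers leaves controls room to increase, so a definition is possible. It has simply not been given, for any arm.

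A reader might also infer from the printed β that the trial was planned at 20% power, or that 91 is wrong. Steps 1 and 2 rule out both. The slip plays no part in the mismatch between endpoint and outcomes.

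Two further replies are fair. The section claims power only for the stated difference and nowhere asserts 80% for metabolic syndrome. And a condensed article may leave a responder definition to a fuller document. The criticism is therefore confined to what is visible here: a stated sample-size basis and a stated outcome list that do not match, and a symbol that is wrong as printed.

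**Conclusion.** The point holds in this form. The arithmetic of 91 per group is right for 30% v 50%, two-sided α = .05 and power .80, and β is mislabelled. The endpoint used is undefined and unlisted. The 80% power therefore does not extend to metabolic syndrome, and it is not shown for weekly frequency as specified.

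It would go too far to say that the calculation lends no support at all to the physical activity outcome. What is missing is the step from responder to weekly frequency.

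The practical weight falls on metabolic syndrome, where only falls of about 17 to 20 points are detectable with 80% power. That range rests on assumed control rates of 30–70% and on 91 analysed men per arm. The 0.42 SD rests on a t-test with the same number.

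**What to change.** Print power = .80 (β = .20).

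Then take one of two routes:
- Define a 12-month responder for all three arms in terms of exercise times per week, list it as an outcome, and justify 30% v 50% for that definition. The rates should not simply be attached to the active-exerciser threshold in the exclusion criteria, because they were not stated for it.
- Restate the calculation on weekly frequency: 91 analysed men per arm detect about 0.42 SD with 80% power by t-test.

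In either case, state that metabolic syndrome was not separately powered, and give the detectable fall (about 17 points from an assumed 30%, about 20 points from an assumed 50–70%) with its assumptions.

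The cost is a rewritten sample-size paragraph and, on the first route, one added outcome. No more patients are needed. The downside is a less favourable stated sensitivity for metabolic syndrome.

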### Statistical analysis

A primary intention-to-treat analysis will be carried out. The main analyses involve standard two-sample comparisons (parametric or non-parametric depending on the distribution of the data) looking at effect sizes at 3 and 12 months.

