## Discussion

In this study, we assess the effects of primary care interventions aiming to reduce cardiovascular risk in early middle-aged men. Health promotion by public health nurses has become a popular method in cardiovascular prevention. Its effectiveness has, however, recently been questioned
[4]. At the onset of this the trial, it was clear that it had to be included it in the intervention. We also wanted to study an exercise intervention, as many cardiovascular risk factors can be controlled through exercise
[12,13].

We chose a group-based intervention because we considered the social support in the group to be an important motivational factor for the success of the intervention. Kirkkonummi is a suburban municipality, where most of the families move from other parts of Finland to work in the capital region. Many men do not have the social networks of their youth for maintaining their exercise activities. One possible result of this trial is that men continue to exercise in their intervention groups. We will follow-up for the potential societal effects of the trial using qualitative methods.

The strengths of this study are that it is a primary care pragmatic trial and that the results are readily generalizable to similar primary care settings. Also, the interventions included are feasible and non-expensive. If they prove effective, they can easily be transferred to other similar circumstances.

The study has some limitations as well. Blinding is not feasible and this study is performed as an open trial. Randomized controlled trials are not common in primary care health centers and there are threats to validity, e.g. how to guarantee similar processes by all study nurses and how to avoid other protocol violations. A special challenge is to keep the participants in the control group. As the participating men are not patients but working-aged and busy, their participation in the outcome measurements is a challenge.

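### Visit-by-visit two-sample tests leave out the 6-month activity data and ignore earlier values of men lost by month 12, although control-arm retention is a named worry

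*Protocol article*

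**What the plan says.** The Statistical analysis section has two sentences. The first reads "A primary intention-to-treat analysis will be carried out". The second names the method and the times (in months): "The main analyses involve standard two-sample comparisons (parametric or non-parametric depending on the distribution of the data) looking at effect sizes at 3 and 12". No repeated-measures model is named.

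The Outcome measures section says "The outcomes are measured after 3, 6 and 12 months of the randomization". Table 1 marks self-reported activity, a primary outcome, at baseline and all three follow-up times. Blood is taken at 0, 3 and 12 months only. Men who do not answer the Internet survey are followed up by telephone.

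On retention the Discussion says "A special challenge is to keep the participants in the control group" and, of the working-aged men in general, that "their participation in the outcome measurements is a challenge". It also says that blinding is not feasible and the trial is open. No expected loss rate appears anywhere. The Sample size section works at the one-year horizon and concludes that "91 men in each group are needed".

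**The concern.** A t-test or rank test at month 12 compares the men who have a month-12 value. Unless something is added, a man with activity recorded at 0, 3 and 6 months but not at 12 contributes nothing to the one-year result, which is the horizon the trial is sized on. His month-6 value is likely to be the best guide to where he was heading, and it is not in the main analysis at all.

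This matters because the authors themselves place the retention difficulty in one arm of an unblinded trial. If less active control men tend to leave, the remaining controls look more active than the randomised arm and the exercise effect is understated. If the more active ones leave, it is overstated. The named method has no means of correcting either case, although data that could help are already being collected.

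**Working it through.** **1. The plan's own figure.** Inputs from the Sample size section: 30% v 50%, α = 0.05 (taken as two-sided), and the stated β of .80 read as power. The unpooled two-proportion formula gives n = (1.960 + 0.842)² × (0.30×0.70 + 0.50×0.50) / 0.20² = 90.3, so 91 per group. The figure reproduces and is not in dispute.

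**2. Scale for activity frequency.** With 91 men analysed per arm, in SD units:
- standard error of the difference = √(2/91) = 0.148 SD;
- difference detectable with 80% power = 2.80 × 0.148 = 0.42 SD.

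**3. Bias when loss depends on month-6 activity.** Assumptions, none of them from the protocol: four normally distributed visits (0, 3, 6, 12 months), every pair correlated 0.5 or 0.7; probability of loss at month 12 logistic in month-6 activity, slope 1 or 2 per SD, with less active men likelier to leave. Very large simulated arms were used, so that bias is seen without sampling noise. Bias in the available-case difference (exercise minus control) at month 12:

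| Loss, control v exercise | Bias (SD) |
|---|---|
| 9% v 9%, same mechanism | about 0 |
| 13% v 7% | about -0.02 to -0.06 |
| 18% v 4.5% | -0.06 to -0.12 |
| 30% v 10% | -0.08 to -0.16 |

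A 20% v 10% pair falls inside the same overall range. Against the standard error, 0.02/0.148 = 0.1 and 0.16/0.148 = 1.1. The sign reverses if the more active men leave.

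**4. The alternative analysis on the same data.** Regression on the 0-, 3- and 6-month values, the missing-at-random equivalent of a repeated-measures model, left bias below 0.01 SD in every scenario of step 3. That is true by construction, because loss was generated from a value the analysis conditions on. The harder test makes loss depend on month-12 activity itself. There the model still leaves about 0.02 to 0.17 SD, roughly 40% to 75% of the available-case bias, so it removes about 25% to 60%.

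**5. The same mechanism on the planning scale.** Suppose the true rate is 30% in both arms, 100 men are randomised per arm, and only controls are lost. Observed control rate = (0.30 - d × p_lost)/(1 - d), where d is the loss and p_lost the success rate of the lost men.
- d = 20%, p_lost = 10%: (0.30 - 0.02)/0.80 = 35.0%, bias -5 points.
- d = 20%, p_lost = 50%: (0.30 - 0.10)/0.80 = 25.0%, bias +5 points.
- In both cases the two-sided error rate is about 11% instead of 5%.
- d = 10%, same p_lost range: bias ±2.2 points, error about 6%.
- p_lost = 30%: bias 0, error 5%.

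**The case against.** A reader might infer that the plan contradicts its own intention-to-treat label, or that men without a measurement are bound to be excluded. The text supports neither. Analysing men as randomised is compatible with a two-sample test, and such a test can follow imputation or a non-responder rule. The wording about what the main analyses involve is not exclusive. A journal article may leave missing-data rules to a fuller plan, so silence on them is no fault, and nothing is claimed here about imputation for metabolic syndrome.

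A reader might also treat the gap between 300 recruited and 3 × 91 = 273 as a planned allowance of 27 losses, or the Discussion as a forecast of control-arm loss. The protocol states no allowance and no rate, and it links no loss to outcome.

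Other points on that side stand. Months 3 and 12 are the follow-up times when blood is taken, so choosing them is reasonable, and omitting month 6 does not in itself bias either contrast. Telephone follow-up protects the very outcome simulated above, so real loss of activity data may be smaller than assumed. A model that uses men with any follow-up value still leaves out those with none.

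What the objection does not remove is that the article goes beyond silence. It names a method and two time points, and that method, as named, uses neither the repeated measurements nor the 6-month activity.

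**Conclusion.** The point holds as a weakness in the chosen method for one primary outcome, physical activity frequency. The possible bias at 12 months is about 0.02 to 0.16 SD under the assumed unequal losses that depend on month-6 activity. That runs from negligible to about one standard error, in an unknown direction. It is near zero if loss is equal with the same mechanism in both arms, or is unrelated to activity. Loss rates, correlations and loss mechanism are all assumptions. A repeated-measures model removes the bias only under missing at random and reduces it partly otherwise. The 6-month point does not extend to metabolic syndrome: Table 1 marks that outcome at T2, but no blood is taken at 6 months. The change is worth making because it is cheap; the stated plan is not thereby invalid.

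**What to change.** In the Statistical analysis section, for physical activity frequency, make the main analysis one likelihood-based repeated-measures model: a linear mixed model, or a Poisson or negative binomial mixed model if the weekly counts call for it. Use the 3-, 6- and 12-month values of all randomised men with any follow-up value, with the baseline value and arm-by-visit terms. Take the 3- and 12-month contrasts from it, and keep the two-sample comparisons as supportive.

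Add one delta-adjusted sensitivity analysis in which missing men are assumed to be more or less active than the model predicts, with the shift allowed to differ by arm. It should include men with no follow-up value, whom the model does not reach.

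The cost is a few sentences of analysis text and modest programming. No extra visits, data or men are needed, because Table 1 already collects activity at 6 months. The downside is reliance on a missing-at-random model and a result slightly harder to explain than a two-sample test.

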#### Exclusion criteria

– BMI over 34 (or any other physical barrier preventing participation in the exercise intervention)

– Active exerciser (exercising at least 30 minutes 3 times a week or more)

– Having an immediate health problem requiring treatment or a severe risk factor; for example, recently diagnosed or uncontrolled type I diabetes, or a symptomatic coronary artery disease.

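### The stated main analysis leaves out the baseline values of both primary outcomes and lets the data choose the test for exercise frequency, which costs precision and leaves the estimated quantity unfixed

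*Protocol article*

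**What the plan says.** The Statistical analysis section is two sentences long. After stating that the primary analysis is by intention to treat, it says: "The main analyses involve standard two-sample comparisons". The type of test is "parametric or non-parametric depending on the distribution of the data", and the comparisons are described as "looking at effect sizes at 3 and 12 months". No covariate, change score or regression model is named, and no scale is given for the effect sizes.

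Other sections show that baseline values will exist:

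- Abstract, Methods/design: "The participants are assessed at baseline, and at 3, 6, and 12 months".
- Randomization: once "the baseline measurements are carried out, they are randomly allocated to one of the three study groups". Baseline values are therefore unaffected by treatment.
- Outcome measures, Table 1: both primary outcomes are marked at T0. One is listed as "1.1 Metabolic syndrome1 (yes/no)". The other is "self-reported physical activity measured by how many times per week a participant performs vigorous exercise activity".

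**The concern.** Baseline status should predict both outcomes. The Inclusion criteria admit men with and without metabolic syndrome. Total cholesterol above 4.0 mmol/l plus LDL-cholesterol above 3.0 mmol/l is enough for entry, and neither is a criterion of the syndrome. A man with a waist above 94 cm, fasting glucose above 6.1 mmol/l and triglycerides above 2.0 mmol/l already meets three of its criteria. Men who exercise more at entry can also be expected to exercise more at 12 months. A two-sample t test or rank test leaves this predictable variation in the error term.

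The choice of test raises a second issue, for exercise frequency only. A t test goes with a difference in mean times per week, and a rank test goes with a different quantity. If the observed distribution decides between them by an unstated criterion, the target of estimation is known only after the data are seen.

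Precision matters in this trial. The Sample size section asks for 91 men per group. The planned 300 men give 100 per arm if allocation is equal (an assumption), and the Discussion names retention of control men and attendance at outcome measurements as challenges.

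**Working it through.** **1. The plan's own figure.** Inputs from the Sample size section are 30% versus 50%, α = 0.05 (taken as two-sided) and 0.80 (labelled β there, read as power).

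n = (1.960 + 0.842)² × (0.3×0.7 + 0.5×0.5) / 0.20² = 7.849 × 0.46 / 0.04 = 90.3, so 91 per group.

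The figure reproduces with the unpooled formula (the pooled formula gives 93). It is for a binary quantity, the share of men who keep up an increased exercise level. That quantity is neither of the two primary outcomes as defined.

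**2. Exercise times per week.** With baseline as covariate in a linear model, the variance of the treatment difference is multiplied by 1 − r². The documents give no r, so it is assumed. The Exclusion criteria remove any "Active exerciser (exercising at least 30 minutes 3 times a week or more)", which narrows the baseline range and so may lower r. As an illustration under bivariate normality, cutting off the top 20% to 50% of baseline activity turns r = 0.5 into 0.40 to 0.33. The range used is therefore 0.3 to 0.5.

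Formulas, with 100 men per arm:
- Equivalent unadjusted men per arm = 100 / (1 − r²)
- Difference detectable with 80% power, in SD = 2.802 × √(2/100 × (1 − r²))
- Power where the unadjusted test has 80% = Φ(2.802/√(1 − r²) − 1.960)
- Relative variance of a change score = 2(1 − r)

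| r | 1 − r² | Variance saved | Equivalent men per arm | Detectable difference (SD) | Power | Change-score variance |
|---|---|---|---|---|---|---|
| none used | 1 | 0% | 100 | 0.396 | 80% | – |
| 0.3 | 0.91 | 9% | 110 | 0.378 | 84% | 1.4 |
| 0.4 | 0.84 | 16% | 119 | 0.363 | 86% | 1.2 |
| 0.5 | 0.75 | 25% | 133 | 0.343 | 90% | 1.0 |

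**3. Metabolic syndrome.** The factor 1 − r² does not carry over directly to a logistic model, so a worked case is used. Assume 100 men per arm, half with the syndrome at baseline, control risk at follow-up of 25% without and 75% with it at baseline, and a conditional odds ratio of 0.5.

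- Intervention risks: odds 1/3 × 0.5 = 1/6 give 0.143; odds 3 × 0.5 = 1.5 give 0.600.
- Overall risks: 0.500 and 0.371.
- Standard error of the risk difference, unadjusted: √((0.2500 + 0.2335)/100) = 0.070.
- Adjusted, with two strata of 50 men per arm and weight ½ each: √(0.25 × (0.1875 + 0.1224 + 0.1875 + 0.2400)/50) = 0.061.
- Variance saved: 1 − 0.003687/0.004835 = 24%.

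In a simulation of the same case, power rose from 45% to 55% with logistic adjustment, but the standard error of the log odds ratio also rose, from 0.289 to 0.340. Adjustment helps here, but a narrower interval appears on the risk-difference scale and not on the odds-ratio scale.

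**4. Choice of test.** In a simulation with no true effect (100 per arm, 6000 runs, nominal 5%), choosing between the t test and the Mann-Whitney test by a Shapiro test gave a type I error of 5.4% for normal data and 5.0% for skewed counts. Taking the smaller of the two p-values gave 6.1% and 6.7%, but the plan does not propose that.

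**The case against.** The strongest reply is that a short article need not list covariates. The text nowhere calls the comparison unadjusted or limited to follow-up values, and a two-sample comparison of change from baseline would fit the words. An analysis plan that is not shown may supply the model.

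Part of this stands: the missing detail alone would be no finding. But the section does name its method, and a two-sample t or rank comparison has no place for a covariate. A later plan would have to depart from the stated method, not just fill it in. The change-score reading is possible but unstated, and for r up to 0.5 it is no more precise than follow-up values alone (last column of the table).

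It can also be said that the unadjusted comparison is valid and that its confidence interval already allows for chance imbalance. Both points are right, and they limit the finding to efficiency. A rank analysis can also report a shift in times per week (Hodges-Lehmann), so a rank test does not rule out an effect in natural units. It is still a different quantity from the mean difference.

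A reader might go further in four ways that the documents do not support:

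- **Bias.** Baseline precedes random allocation, so leaving it out does not bias the comparison.
- **A saving applied to the 91.** Scaling 91 by 1/(1 − r²) gives 121 men at r = 0.5. The 91 belongs to a binary endpoint that has no baseline value, since nobody can be continuing an increase at T0. The scaling is not valid.
- **Narrower intervals whatever the scale.** For the odds ratio, adjustment raised the standard error in the worked case even though power rose.
- **Inflated false-positive risk.** The plan ties the choice of test to the distribution, not to the treatment contrast, and that rule stayed near 5%.

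**Conclusion.** The point holds as a free improvement to a valid analysis. Both primary outcomes are measured before allocation, and the stated main analysis uses neither baseline value. For exercise times per week, the avoidable variance is about 9% to 25%. This rests on an assumed r of 0.3 to 0.5. It also assumes that excluding active exercisers narrows the vigorous-exercise count; the exclusion is worded in terms of 30-minute sessions, so the match is not exact. For metabolic syndrome a gain in power is expected, but its size depends on how strongly baseline status predicts follow-up. The 24% above is illustrative only.

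The data-driven choice of test concerns exercise frequency alone. Its cost is that the quantity to be estimated is not fixed in advance. For the yes/no outcome that choice does not arise; the gap there is that the named method has neither a baseline term nor an effect measure.

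**What to change.** In the Statistical analysis section, replace the two-sample wording with one named model and one effect measure per primary outcome:

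- **Exercise times per week at 12 months:** ANCOVA with baseline times per week as covariate and robust standard errors, whatever the distribution. Report the adjusted mean difference with 95% confidence interval. Keep a rank test as a sensitivity analysis.
- **Metabolic syndrome at 12 months:** one baseline-adjusted model with one collapsible measure, chosen now. Examples are the risk difference by standardisation after logistic regression, or the risk ratio by modified Poisson regression. Use metabolic syndrome status at T0 (or the number of criteria met at T0) as covariate and report a 95% confidence interval.

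The same models can serve the 3-month comparisons. The sample size of 91 should not be rescaled on this account. The cost is analysis wording only, since every covariate is already collected at T0.
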